## Abstract

**Background:**

Depression is a major public health concern. E-health interventions for preventing and reducing depressive complaints have proven to be effective, and have the potential to make (mental) health care more accessible and efficient. However, the reach of these interventions needs to be improved, especially among people with a lower socioeconomic status (SES). Stimulating and supporting implementation of e-health in primary care, and offering guidance from general practice nurses (GP nurses) may be important strategies to achieve this.

**Methods/design:**

The online ‘Complaint Directed Mini-Interventions’ (CDMIs) for stress, sleep and worry complaints, which were found to be (cost-)effective in a self-guided format, will be implemented in the primary care setting using a blended care format (i.e. combining e-health with face-to-face sessions) with minimal guidance provided by the GP nurse. The main aim is to evaluate whether a SES-sensitive implementation strategy improves the participation rate (i.e. reach) of lower-SES patients in the blended online CDMIs as compared to a regular implementation strategy in a cluster randomised controlled trial. Randomisation will occur at the level of the GP nurse, and 228 patients will be included in the study. The primary outcome is the participation rate (completing at least one face-to-face session and two online exercises) of the lower-SES target group. It is hypothesised that this percentage will be higher in the SES-sensitive group as compared to the regular group. Secondary objectives are to evaluate the implementation process, to monitor and evaluate psychological complaints (depression, sleep, stress, worry and anxiety) and well-being over time. Patient assessments will take place at baseline, 3 and 12 months post baseline.

**Discussion:**

This study should contribute to our knowledge of reaching the lower-SES groups with a brief and complaint-specific blended approach for depressive complaints in primary care. It should also further our knowledge on successful strategies to implement depression prevention in primary care.

**Trial registration:**

Netherlands Trial Register, ID: NL6595. Registered on 12 November 2017.

## Background

Depression is a major public health concern associated with individual suffering, impaired functioning and substantial societal costs [1–3]. There is growing evidence that interventions targeting (symptoms of) depression are effective, and that preventing and reducing depressive symptoms could be a viable option [4]. However, the reach of these interventions is only modest, especially among people with a lower socioeconomic status (SES) [5–7]. This is of importance as people with a lower SES seem to be particularly at risk for depression. In the Netherlands, for example, the life-time prevalence of depression is higher among those with a low income (21.4%) as compared to those with a high income (15.2%) [8].

However, e-health interventions (interventions offered over the Internet) for depression and depressive symptoms may reach large populations. These interventions are more accessible and more flexible in use than regular face-to-face interventions. Nonetheless, participants in online interventions are primarily highly educated [9], while those with lower education levels are reached to a lesser extent. This implies that those with a medium or low educational level are not reached as widely with these interventions. If uptake is achieved, evidence shows that adherence to online interventions needs improvement [9–11], especially if these interventions are to make a greater impact on population health. Although self-guided online interventions can be effective, providing guidance to patients may improve not only adherence, but also the effectiveness of such interventions [12–14]. Embedding (preventive) online interventions for depressive complaints in routine care combined with guidance from a health care professional may also provide an important strategy for implementing available online interventions among lower-SES populations.

In Dutch primary care, it is the task of the general practitioner (GPs) to provide mental health care in case of mild to moderate mental health complaints. The GP mental health nurse (GP nurse), who works alongside the GP, plays a pivotal role in delivering mental health care in the GP setting. Because the GP nurse focusses on mental health and provides longer consultations than GPs, the GP nurse is well-placed to offer guidance in e-health interventions for depression. Moreover, GP nurses report a favourable attitude towards e-health and may already offer some type of e-health intervention for mental health [15, 16]. Nonetheless, GP nurses indicate that there is room for improvement. One frequently mentioned problem is the lack of suitable e-health interventions, specifically for low-educated patients. In addition, GP nurses prefer interventions that can be tailored to the patient’s personal complaints which is often not possible in current standardised (one-size-fits-all) interventions. Early dropout of patients and too few possibilities to familiarise themselves with e-health interventions were other frequently mentioned problems [16]. In sum, e-health interventions need to be integrated in the GP setting and need to be matched better to the personal needs of patients, in order to reach more patients, especially those with a lower SES.

In the present study, the online ‘Complaint Directed Mini-Interventions’ (CDMIs), which were found to be (cost-)effective in a self-guided format [17, 18], will be implemented in the primary care setting using a blended care format (i.e. combining the e-health intervention with supporting face-to-face sessions that will be provided by the GP nurse). The online CDMIs are short, low-threshold unguided web-based interventions that target depressive complaints by focussing on highly prevalent complaints that are demonstrably associated with depression and have a substantial economic impact: stress, sleep problems and worry [19]. There are three different CDMIs: ‘Sleep better’, ‘Stress less’ and ‘Worry less’, and each CDMI contains various modules and exercises (see [18] for more information). A feature of the CDMI intervention framework is that patients can choose the complaints that they want to focus on (by choosing the CDMIs that they want to use), and it also allows patients to choose the modules and exercises that they want to do and in what order (pick and mix). The CDMIs are based on cognitive-behavioural techniques as well as elements from solution-focussed therapy, mindfulness and positive psychology. They were developed to be as easy to understand and use as possible. They are focussed on ‘doing’ rather than ‘reading’ with the aim to appeal to a broad range of people, including those with a lower educational level. However, in line with other studies of e-health interventions for depression [9, 20], mainly individuals with a high education level or income participated in the randomised controlled trial (RCT) of the self-guided format (more than 70%). This indicates that there is a clear need for implementation strategies that increase the reach of e-health interventions for depression, including the CDMIs, particularly among lower-SES groups. They may particularly benefit from a more proactive strategy [21], including more proactive and intensive guidance, and additional strategies that take the specific needs of this target group into consideration such as low(er) health-literacy skills [22, 23]. Therefore, a SES-sensitive implementation strategy will be developed in collaboration with primary care professionals and patients, and will be compared to a regular implementation strategy in a randomised controlled trial.

## Methods/design

This protocol was developed in accordance with the Standard Protocol Items: Recommendations for Interventional Trials (SPIRIT) Statement. See Additional file 1 for the SPIRIT Checklist.

### Aim

The aim of this study is to evaluate whether a SES-sensitive implementation strategy to implement the online CDMIs in primary care improves the percentage of lower-SES participants as compared to a regular implementation strategy. The hypothesis is that the percentage of lower-SES participants in the online CDMIs will be higher in the SES-sensitive implementation strategy group as compared to the regular implementation strategy group.

### Design

A pragmatic cluster randomised controlled trial with two parallel groups will be conducted in which the two implementation strategies will be compared. As the GP nurse plays a key role in the implementation strategies, randomisation will take place at the level of the GP nurse in order to avoid contamination between the two implementation strategy conditions. Thus, each GP nurse will be randomised to one of the two implementation strategy groups. GP nurses cannot be blinded to the implementation strategy that they are allocated to because they will be aware whether their allocated implementation comprises specific components aimed at reaching lower-SES patients. The randomisation status will not be disclosed to patients. It is worth noting that the online CDMIs will be implemented in both conditions, meaning that the intervention will not be withheld from any patients participating in the study. Moreover, patients are free to receive any other type of care during the study. Participating patients will be assessed at baseline (T0), 3 months after baseline (T1) and 12 months after baseline (T2). Assessments among participating GP nurses will take place at two time points: at baseline, and 6 months after baseline. See Fig. 1 for the flowchart of the study and Table 1 for an overview of the schedule of enrolment, interventions and assessments in accordance with the SPIRIT Statement. This study is registered at the Netherlands Trial Register (NL6595) and was approved by the Medical Ethics Committee of the VU University Medical Center.

**Fig. 1 Fig1:**
[figure not shown]
Flowchart of the study

**Table 1 Tab1:**
[figure not shown]
Schedule of enrolment, interventions and assessments

### Randomisation

Randomisation will be carried out by an independent statistician using a computer-generated schedule. Randomness will be assured by the use of true random numbers of Random.org (https://www.random.org). Randomisation will be stratified for the SES (low SES, medium SES, high SES) of the neighborhood in which the GP nurses work in order to balance the distribution of this factor across the two study groups. The SES status level of the neighbourhood (low SES, medium SES, high SES) will be used as the stratification variable. The neighborhood SES level is linked to the four-digit postal codes of the neighbourhood where the GP nurse works and matched to the 2016 social status scores as determined by the Netherlands Institute for Social Research [24].

### Eligibility criteria and recruitment

#### GP nurses

GP nurses from two organisations will participate in this study. One of the organisations is a primary care health service provider in the Almere region of the Netherlands. It elected to participate in this study with the whole organisation (all primary care practices and their GP nurses). The other organisation provides GP nurses serving GP practices in the Rotterdam-Rijnmond area of the Netherlands. This organisation recruited GP nurses willing to participate (via email) after members of the research team gave a short presentation about the study. The GP nurses will recruit patients from the general care practice(s) where they work according to the implementation strategy (i.e. the regular or SES-sensitive implementation strategy) to which they were randomly assigned.

#### Patients

Primary care patients of the GP nurses involved in the study are eligible for participation, when they:
Are 18 years of age or olderExperience worry, stress or sleep problems (the latter without a medical cause such as sleep apnea as ascertained by the GP or GP nurse)Have access to the InternetHave sufficient proficiency of the Dutch languageHave no acute or urgent comorbidityProvide informed consent.

In view of the recently published report about the risk of including suicidal patients in RCT studies [25], we will not exclude patients with suicidal ideation. However, suicidal thoughts will be assessed at baseline, after 3 and after 12 months. To this end, item 15 of the Web Screening Questionnaire (WSQ) will be used [26]. This question is comparable with item 9 of the PHQ-9, but the answers give more detail about the degree of active suicidal ideation, which is not well reflected by item 9 of the PHQ-9 [27]. The item is scored on 4-point scale (0 = definitely not, 3 = I would do it given the opportunity). If participants score 3 on this item they will be advised to discuss the suicidal thoughts with their GP nurse or to contact the anonymous online platform for people with suicidal thoughts or behaviours (www.113Online.nl). The GP nurses can check the answer of this item in the CDMI monitoring system (see below).

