#### Inclusion procedure

The GP nurse will inform eligible patients about the online CDMIs and the study during a consultation. If the patient shows interest in participating, the GP nurse will hand over an envelope with: (1) an information brochure about the online CDMIs and (2) an information letter about the study. In addition, the GP nurse will send an invitation to the patient to participate in the online CDMIs by email (sent from the monitoring system). The patients will subsequently receive an email with information about the study and are asked if they are willing to participate in the study. If this is the case, they can click on a button which directs them to the informed consent form. They can then provide consent by clicking on the ‘I consent’ button. Following this, the patients are directed to a webpage where they can create their own online CDMI account by providing their email address, password and gender. After logging in to the online CDMIs for the first time they will be asked to complete the (online) baseline questionnaire. Data collected for research purposes will be stored in a database using a unique respondent number for each individual patient. Email addresses will be stored in a separate database on a separate server. Data will also be used for clinical purposes within the monitoring system. Data processing agreements will be put in place with the relevant parties, besides the research team, who have access to the data for this purpose (ICT parties/monitoring system provider and primary care organisations). Patients who indicate that they do not wish to participate in the study are offered the opportunity (by clicking on a link) to use the self-help version of the online CDMIs (without the GP nurse being able to monitor progress and provide guidance using a monitoring system). The flowchart of the study is presented in Fig. 1.

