#### Monitoring system

To facilitate the implementation of the blended CDMI format in primary care, the online CDMIs will be linked to a monitoring system allowing the GP nurses to check on the patient’s progress when using the CDMIs and to track complaints over time. The monitoring system will provide the GP nurse with insight into the intervention use of their patients (e.g. answer to questionnaires, diary entries, number of logins, number of completed exercises), and allows them to send messages to their patients.

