#### Implementation strategies

Successful implementation of e-health is not only related to the patient-related factors, but also to the intentions and motivations of health care providers and their management [28, 29]. This means that GP nurses play a crucial role in the implementation process. In this study, the main focus of the implementation strategies is aimed at the GP nurses and the patients. That being said, management-level representatives of the two participating organisations will be actively involved during the implementation process and will also be members of an Advisory Committee that will be installed for the purpose of this project. This will allow for an ongoing dialogue about relevant organisational aspects and possibilities for (organisational) support or even change throughout the implementation process. The main aim of the Advisory Committee is to advise the project team on a range of content- and implementation-related issues in order to facilitate the execution of the project. Their role is thus advisory: their suggestions will be carefully considered, yet they do not have decision-making power. Besides the representatives of the participating organisations, members of the Advisory Committee will be independent of the trial. Given the goal of our project to compare two implementation strategies for the online CDMIs (an intervention that has been studied in a previous trial), and the implementation-related primary outcome of this study, we did not install a data monitoring committee. A DMC was also not part of the approved protocol.

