##### Regular implementation strategy

Prior to the start of the study, the research team will visit the implementation locations and give a presentation during GP nurse team meetings to garner interest in, and support for, the study.

Participating GP nurses who have been randomised to the regular implementation strategy will then be invited to attend a 2-h training in which they will:
▪ Learn about the online CDMIs, the related monitoring system and guidelines for the recruitment and guidance process▪ Practice using the online CDMIs and its monitoring system▪ Discuss possible barriers and facilitators for implementation

To be able to tailor the guidance to specific individual needs of patients, GP nurses in the control condition will be free in the amount of guidance they give. The only requirement is that they provide at least one face-to-face consultation. However, the basic advice suggested in the implementation manual is to schedule 3 consultations: at the start, midway and at the end of the period in which the CDMIs are used by the patient. It is also up to the GP nurses whether or not to recommend certain modules or exercises within the CDMIs. During the training general guidelines for topics that can be discussed during the consultations (e.g. what kind of instruction to give about the online CDMIs, discussing the diary, giving compliments) as well as indicating potential (motivational) barriers of patients to initiate and maintain usage of the online CDMIs. The GP nurses will be provided with a manual with information on all the topics covered during the training. After a practice period of approximately 2 months, the GP nurses will be invited to participate in a follow-up session, led by the research team, to exchange experiences and discuss potential problems that arose during the practice period.

The research team will provide ongoing support to the GP nurses throughout the implementation period in several ways:

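### The top suicidality answer triggers advice to the patient, while the GP nurse may look at it but nothing shown requires any clinician to see it, at baseline, 3 or 12 months

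*Protocol article*

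**What the plan says.** The Patients section (under Eligibility criteria and recruitment) states that "we will not exclude patients with suicidal ideation". It pairs this with item 15 of the Web Screening Questionnaire, asked at baseline and after 3 and 12 months and scored 0 to 3. A score of 3 means that the respondent would act on the thoughts if the chance arose. Such patients are advised "to discuss the suicidal thoughts with their GP nurse or to contact the anonymous online platform". The nurse's part is one sentence: "The GP nurses can check the answer of this item in the CDMI monitoring system (see below".

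Other sections bear on this:

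- Patients: acute or urgent comorbidity rules a patient out.
- Design: patients may receive any other care during the study.
- Inclusion procedure: the nurse raises the study in a consultation. Invitation, consent and account creation follow, and then "After logging in to the online CDMIs for the first time they will be asked to complete the (online) baseline questionnaire". The section adds: "Data will also be used for clinical purposes within the monitoring system".
- Monitoring system: nurses can see questionnaire answers, message patients and "track complaints over time".
- Regular implementation strategy: one face-to-face consultation is required. Three are advised, "at the start, midway and at the end of the period in which the CDMIs are used by the patient".

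**The concern.** Repeated questioning is what the article sets against the decision to admit patients with suicidal ideation. The item was chosen because it separates degrees of active ideation better than item 9 of the PHQ-9. A safeguard of this kind works only if someone who can act on the answer sees it. As stated, that depends on the patient coming forward or on the nurse choosing to look. One of the two routes offered to the patient is anonymous, so taking it need not bring the answer to the nurse. What is at stake is the safety of individual patients, not the comparison between implementation strategies.

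**Working it through.** No calculation applies. The check was to read the article for any text that obliges someone to read, be alerted to, or act on a score of 3.

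**1. Is there a duty in the section that sets the rule?** No. The Patients section states the trigger (score 3), the action (advice to the patient) and the nurse's position (access). The verb is permissive, and no alert, time limit or follow-up contact is attached.

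**2. Does another section add one?**

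| Section | What it provides | Duty to see a score of 3? |
|---|---|---|
| Design | Freedom to use other care | No |
| Inclusion procedure | Clinical use of data, in general terms | No; names no reader and no action |
| Monitoring system | View of answers, messaging | No; a facility, with no alert described |
| Regular implementation strategy | One required consultation, three advised | No; timed by use of the intervention |
| Table 2 | Interim and final evaluation within flexible guidelines | No; about progress and the intervention process |
| SES-sensitive implementation strategy | More frequent contact advised, extra help with registration and exercises | No; contact is for guidance |
| Fidelity and adherence | Nurse reports on guidance given and number of consultations | No; process data |

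**3. Which assessments are affected?** The item is asked at 0, 3 and 12 months, and one rule covers all 3.

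- *Baseline.* Guidance is just starting, so the nurse is likely to be in touch. However, the questionnaire follows the recruiting consultation, consent and account creation. The answer therefore arrives after the nurse has treated the patient as eligible, and the comorbidity criterion cannot be relied on to catch it.
- *3 and 12 months.* The one required consultation in the regular arm may have taken place at the start. The extra contacts in the SES-sensitive arm are advised, not required at these times. No nurse contact is therefore required around 2 of the 3 assessments.

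**4. Can the plan be followed with the answer unseen?** Yes. Suppose a regular-arm nurse holds one consultation at the start, and the patient scores 3 at 12 months, receives the advice, and either does nothing or uses the anonymous service. Everyone has done what the article asks, and no clinician need have seen the answer.

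**5. How many patients?** The article gives no rate of score 3, so no count or range can be derived from it.

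**The case against.** The strongest reply is that this is a condensed article. It refers to an approved protocol (version 1.0) and a nurse manual, neither of which is shown, and either could say who opens a flagged answer and how fast. It can also be said that the sentence merely describes what the system allows and does not declare checking optional. The setting is favourable too: these are the nurse's own patients, recruited in a consultation, free to seek other care, with their answers already in a system the nurse uses. An ethics committee approved the study.

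Much of this stands and limits the point. It does not remove it, because the article does not leave the response to later documents. It states trigger, action and nurse's role, and the role as stated is permissive.

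Four stronger readings are tempting and are not supported:

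- *Nobody will see these answers.* Nurses have access and may well look. Only the obligation is absent.
- *There is no nurse contact around 3 or 12 months.* The advised consultations are timed by use of the intervention, whose length is not stated, so one may fall near 3 months. That contact is not required does not show that it will not happen.
- *The gap exists only at follow-up.* The rule is identical at baseline; only the likely exposure differs.
- *The lack of a data monitoring committee is part of the fault.* The article says "we did not install a data monitoring committee" and gives its reasons. Nothing in it suggests that such a committee would act on one patient's item score.

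**Conclusion.** The point holds as a patient-safety matter that should be corrected. At all three assessments, the stated response to the most severe answer is advice to the patient plus optional access for the nurse, and nothing shown requires a clinician to see it. Exposure is greatest at 3 and 12 months.

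The conclusion rests on the article alone. If the approved protocol or nurse manual already makes the check mandatory, what remains is an inaccurate sentence in the article. Confidence is moderate for that reason. The number of patients concerned is unknown, and the primary estimate of lower-SES participation is unaffected.

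**What to change.** Replace the permissive sentence with a required step that applies at baseline, 3 and 12 months:

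1. A score of 3 sends an automatic notice from the monitoring system to the patient's GP nurse. If this cannot be configured, the nurse must check the item after each questionnaire.
2. The nurse contacts the patient within a short time stated in the protocol. The GP does so if the nurse is no longer involved. Without this step, a notice would only move the gap one stage along.
3. The patient information says that the nurse will be informed of such an answer.

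The advice to the patient stays. If the approved protocol or manual already contains these duties, state them in this sentence instead.

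**Cost.** The change uses data already in the nurse's system and existing staff. It needs a small configuration change or a mandatory check, and there will be occasional notices to handle (number unknown). An ethics amendment is probable, since recruitment began in January 2018. Recruitment was expected to end in June 2019, so the last 12-month questionnaires fall around June 2020 (June 2019 + 12 months), and later assessments could still benefit. Some patients may answer less candidly once they know that the nurse is told. That loss is limited because the nurse can already open the answer.
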